#### Intervention

The intervention programme will be a 12-month multi-disciplinary programme with weekly group sessions. It will be administered by a physical activity coordinator, community dietitian, and psychologist: all staff members within the Whanau Pakari team. It will involve:Home visits with the dietitian and physical activity coordinator in the initial phaseWeekly contact in activity sessions of either physical activity ORPsychology sessions (covering topics such as bullying, self-esteem, parenting, making lifestyle changes), and dietitian sessions (covering topics such as portion size, virtual supermarket tours, healthy food on a budget, and vegetable gardens) (Table 3).

**Table 3 Tab3:** Support provided to each group of trial participants enrolled in Whanau Pakari

	Control (Current “standard care”)	Intervention
6, 12, 18, 24 month assessments with nutrition advice and feedback (blood tests at baseline, 12, 24 months)	✓	✓
Home visit within 1^st^ month from physical activity coordinator and dietitian		✓
Physical activity coordinator/Dietitian review of progress at 6 months (seen at group)		✓
Questionnaire review (team), multi-disciplinary team meeting – review and action of alerts	✓	✓
+/− Keyworker		✓
Weekly activity and education sessions for 12 months		✓
Total home visits over 2 years	5	6

The participants will be engaged in the programme one hour per week for four school terms (equating to a total of 40 sessions). The same programme will be delivered to all participants, however these will be tailored to meet the cultural requirements of participants, for example, sessions that include traditional Maori games, recipe makeover of dishes from different cultures, and honouring of particular dietary requirements in cooking sessions. A committed family member will be required to attend to support and learn alongside the child/teenager, as the programme is family-focussed. No incentivisation will be provided for attending sessions. A commitment contract will be signed at entry to the programme, outlining expectations of attendance at a minimum of 70 % of sessions to gain the most out of the programme. After 12 months, families will be linked into local sport centres/aquatic centres/gym facilities.

#### Non-intervention

The non-intervention (control) group will receive the same home-visit model and assessments as the intervention group, but will not undertake any of the intervention sessions (Table 3). The families will receive feedback from the assessments with dietary and physical activity guidelines. This model was chosen for community acceptability and is very similar to what is currently considered ‘standard care’. This group are offered the intervention after 24 months. All participants declining intervention and those who have completed intervention and 12 month follow-up will be discharged back to primary care, with a guideline sheet of what to monitor, and assess with regard to weight-related comorbidities. Any participants withdrawing from the trial before the end of the 24 months will be incentivised to participate in a modified assessment to allow measurement of their progress, thus maximising completeness of data for the intention to treat analysis.

### Randomisation

At baseline, there will be 2 assessments of RFC (given it is not known if a quantitative tool will be successful): the clinician’s subjective measure (ranked pre-contemplation, contemplation, preparation/action), and a specifically devised questionnaire using a 5-point Likert scale that is completed by the child (if > 11 years of age) and a second one for the parent. The RFC questionnaire was based on the original readiness to change questionnaire [15], focussing on beliefs and behaviour around three factors: weight, eating habits and activity levels. If the RFC ranking is scored in the contemplative or further along on either scale, then participants will be offered entry into the trial. We purposely set the bar low (i.e. below the preparation/action level) to assess whether degree of RFC predicts outcomes within those contemplative or above.

Patients will be assessed, consented, and entered into the trial prior to randomisation. Randomisation by minimisation (using age and ethnicity) will be conducted using the Minim randomisation computer programme which maintains approximate balance in the 2 arms for age and ethnicity but incorporates a random element so it cannot be predicted which study arm the subject will be allocated to.

### Primary outcome

The primary outcome measure is the change in BMI SDS in the intervention group compared with the control group recorded at 6, 12, 18 and 24 months post enrolment.

### Secondary outcomes

Secondary outcomes include changes in health-related quality of life; dietary knowledge and behaviour; physical activity (specifically moderate to very vigorous physical activity), sedentary behaviour, knowledge of benefits of physical activity, cardiovascular and metabolic profile (blood pressure, resting heart rate, waist circumference and WHtR) all at 6, 12, 18, and 24 months, and glycaemic control (fasting glucose and HbA1c), fasting insulin and lipids at baseline, 12 and 24 months.

### Other aims and outcomes

This study also aims to investigate whether those assessed as ready for change (i.e. preparation/action) experience a greater reduction in BMI SDS compared with those less ready for change (i.e. contemplation). If the intervention is found to be effective, a cost-effectiveness analysis will be undertaken, taking into account multiple outcome parameters.

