### Statistical considerations

#### Sample size

With 107 participants per group (120 to account for a 10 % dropout rate) there is 80 % power to detect a difference in change in BMI of 0.5 SDS at the 5 % level of significance, with a standard deviation of 1.3 [48]. Of note, only 15/54 lifestyle studies included in a systematic review at the time of study design reported power calculations [11]. Subsequent meta-analysis of interventions has shown that even a change of −0.1 BMI SDS can lead to improvements in cardiovascular and metabolic outcomes [12]. It is hoped that even demonstrating smaller differences as this more recent literature has shown will still be important at a population level.

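### The cost-effectiveness analysis is planned only if the intervention is found effective, a condition that is undefined and selects the effect estimate upward

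*Protocol article*

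**What the plan says.** The only plan for an economic analysis in the protocol article is one sentence under Other aims and outcomes: "If the intervention is found to be effective, a cost-effectiveness analysis will be undertaken, taking into account multiple outcome parameters". The article gives no outcome, visit or threshold by which effectiveness would be judged, and no economic analysis free of this condition appears elsewhere in it.

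Three other places bear on the point.

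- Primary outcome defines the between-group comparison of change in BMI SDS at four follow-up visits (6, 12, 18 and 24 months). Data analyses plans an adjusted general linear mixed model over these visits.
- Sample size states that "there is 80 % power to detect a difference in change in BMI of 0.5 SDS" with 107 per group and an SD of 1.3. It then cites a meta-analysis in which a change of −0.1 BMI SDS can bring cardiovascular and metabolic improvement, and adds: "It is hoped that even demonstrating smaller differences as this more recent literature has shown will still be important at a population level".
- The Discussion says that the trial will inform the Ministry of Health and refers to cost-effective use of limited resources.

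**The concern.** Whether a programme is worth its cost is a question about two quantities together, the extra cost and the extra effect, and about the uncertainty of both. A test of the effect alone does not answer it. A small, imprecise benefit may still be worth buying, and a programme that costs more for no gain is also a result a funder needs. Here the extra input is appreciable: 40 weekly sessions and one more home visit than control (Intervention section and its Table 3).

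The condition has a second consequence. If the economic analysis is run only when the effect estimate was large enough to count as a success, the estimate that enters it is, on average, too large. The smaller the true effect, the stronger this selection.

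At stake is the use of the trial by a health funder. After an unfavourable or inconclusive result there is no economic evidence. After a favourable one, the evidence rests on a selected effect estimate. Because the condition is undefined, nobody can say in advance which case will apply.

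**Working it through.** **Inputs, all from Sample size:** "With 107 participants per group"; "120 to account for a 10 % dropout rate"; a difference of 0.5 SDS at 80 % power; "at the 5 % level of significance"; "with a standard deviation of 1.3". The article does not state whether the test is one- or two-sided. Two-sided is assumed because it reproduces the sample size.

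**The plan's own figure.** n per group = 2 × (1.96 + 0.8416)² × 1.3² / 0.5² = 2 × 7.849 × 1.69 / 0.25 = 106.1, rounded up to 107. Allowing for dropout, 107 / 0.9 = 118.9, or 119. The stated 120 is consistent with this.

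**Assumed reading of the condition (not in the document).** Effective means two-sided p < 0.05 in favour of the intervention on BMI SDS at one visit.

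- Standard error of the difference: SE = 1.3 × √(2/107) = 0.178.
- Smallest estimate that passes: 1.96 × 0.1777 = 0.348 SDS.
- Chance of passing at a true difference d: 1 − Φ(a), with a = 1.96 − d/SE.
- Mean estimate among trials that pass: d + SE × φ(a) / [1 − Φ(a)].

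Worked for d = 0.1: a = 1.96 − 0.1/0.1777 = 1.397. The chance of passing is 0.081. The mean estimate is 0.1 + 0.1777 × 0.1503/0.0812 = 0.429.

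| True difference (SDS) | Economic analysis exists | Mean estimate if it exists | Ratio to truth |
|---|---|---|---|
| 0.1 | 8.1 % | 0.43 | 4.3 |
| 0.15 | 13 % | 0.44 | 2.9 |
| 0.25 | 29 % | 0.46 | 1.8 |
| 0.5 | 80 % | 0.56 | 1.1 |

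The pass rates count only results in favour of the intervention. Two-sided power at 0.1 is 8.7 %, but the difference between the two figures is significant results in favour of control, which would not meet the condition.

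**Sensitivity at a true difference of 0.1 SDS.**

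- If success at any of the four visits counted, the chance of passing is at most the sum of the four: 4 × 8.1 % = about 32 %.
- With a smaller SD of change (assumed values), the pass rate and the mean estimate after selection are 15 % and 0.27 at SD 0.8, 31 % and 0.18 at SD 0.5, and 68 % and 0.12 at SD 0.3.
- The planned adjusted mixed model would also raise the pass rate. The document gives no figures from which to compute by how much.

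The upward selection shrinks as the SD falls but does not vanish: 0.18/0.1 is still 1.8 times the truth at SD 0.5, and 0.12/0.1 is 1.2 times at SD 0.3.

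**The case against.** The strongest reply is that the article never equates effectiveness with one significance test at one visit. It names four visits and an adjusted model, so the 8 % figure and the 4.3-fold ratio are not fixed by the document. This stands: they illustrate one reading, with SD 1.3. A reader might infer that the economic analysis would hardly ever exist for small effects. The document does not support that as a general statement, since other readings or a smaller SD give clearly higher rates.

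A reader might also infer that the protocol contradicts itself by calling a between-group difference of 0.1 SDS important and then shutting it out of the economic analysis. Sample size does not go that far. It reports that a change of −0.1 can bring improvement, without calling this a between-group difference, and it expresses a hope about smaller differences that are demonstrated. A demonstrated difference could well meet the condition. Low power at 0.1 SDS comes from the sample size and is not created by this sentence.

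Nor is every resulting economic analysis badly inflated. At the design difference of 0.5 SDS the ratio is only 1.1, and nothing prevents the analysis from carrying the uncertainty of the effect. The reference to several outcome parameters does not license reporting only the favourable one, and naming a single main effect measure is detail that an article may leave out. Intention-to-treat is already stated under Treatment effects.

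Finally, effectiveness first and cost-effectiveness second is an openly stated sequence for an additional aim. That limits the weight of the point but does not answer it: the sequence still withholds economic evidence after an inconclusive result and still selects the estimate after a favourable one.

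**Conclusion.** The point holds as a minor improvement. The document states the condition explicitly, so this is not a matter of detail left to a fuller plan. It leaves the criterion undefined, and conditioning on a favourable result selects the effect estimate upward. That direction holds for any criterion that favours larger estimates.

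The size depends on assumptions. With significance at one visit, 107 per group and SD 1.3, the selection is slight at 0.5 SDS and large at 0.1 SDS. How often the economic analysis would exist at 0.1 SDS is not determined by the document. It is about 8 % on that reading and about 31 or 32 % with SD 0.5 or with any of the four visits counting, and it would be higher with a still smaller SD. The primary and secondary effectiveness analyses are not affected.

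**What to change.** In Other aims and outcomes, replace the conditional sentence with a statement that the cost-effectiveness analysis will be done whatever the effectiveness result. It should use the estimated intention-to-treat difference in BMI SDS and the costs, with their joint uncertainty. Defining effective in advance would remove the ambiguity but not the selection, so dropping the condition is the better change.

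The cost is analyst time if the primary result is null, plus resource-use data recorded during the trial. The article does not describe how resource use is recorded, but the conditional plan needs the same records, because the result is not known while they must be collected.

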### Data collection

The Healthy Lifestyles Coordinator will collect all data (apart from physical activity assessments) in the home assessments.

All data from assessments will be entered into a specific purpose-built database, which will be reviewed monthly for data validity and completeness. This database includes alerts for data outside acceptable medical parameters, for example, elevated blood pressure percentiles, for discussion at multi-disciplinary meetings.

Progress will be captured on the multi-disciplinary team meeting database page, so the team can review the results of each 6-month assessment for each participant, and make further recommendations or referrals.

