“Whanau Pakari” means “healthy self-assured families that are fully active” in Maori, and was the name gifted to the trial by a prominent Maori community representative. The trial assesses a new mainstream clinical service delivered in an innovative way in order to improve access for Maori, and those from lower socioeconomic backgrounds. Previous child obesity services in the region involved the traditional model of medical referral to a Paediatrician, sometimes with the addition of dietitian input, and physical activity programme input. The physical activity programme, run in the community through the regional sports trust with a maximum number of participants per year, did not specifically target high-risk groups, and was not region-wide [6]. The new programme removes the “hospital visit”, but participants continue to receive support and oversight from a Paediatrician. This multi-disciplinary programme incorporates three novel approaches:It provides a trained roving community coordinator to meet families in their homes, enabling improved access to the clinical service, especially for Maori.It assesses “readiness for change” both quantitatively and qualitatively.It provides follow up to 12 months post intervention to assess persistence of lifestyle changes, which is longer than any other multi-disciplinary obesity intervention model trialled in New Zealand.

There is a clear need for evidence-based interventions for child obesity that demonstrate on-going effectiveness [11]. Whether engaging with those that are more motivated to make lifestyle changes is a strategy that warrants further exploration. Our objectives are firstly, to undertake a multi-disciplinary intervention, which is accessible and appropriate for those most affected by child obesity. Secondly, we aim to assess whether a quantitative RFC questionnaire is useful in predicting response to the intervention. We hypothesise that in obese/overweight children, assessed as psychologically “ready for change”, delivery of a 12-month multi-disciplinary intervention programme results in a significant reduction in body mass index standard deviation score at 12 months.

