## Methods/Design

Whanau Pakari is an unblinded randomised controlled clinical trial being conducted in Taranaki, New Zealand (population 23,139 children aged 0–15 years, of which 28 % are Maori) [19]. Ethical approval was granted by the Health and Disability Ethics Committee (Ministry of Health, New Zealand; CEN/11/09/054), and the trial was registered with the Australian New Zealand Clinical Trials Registry (ANZCTR: 12611000862943). Locality approval has been obtained from Sport Taranaki, and the Taranaki District Health Board.

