### Recruitment

Recruitment for the trial will be through the service, which is being advertised across Taranaki through multiple channels, including referrer training half-days (training sessions about the service, and how to have conversations about weight with families), meetings (hui) with all stakeholders, general practice visits, school visits, media releases, pamphlet drops at public places and events, and the Public Health Unit of Taranaki District Health Board.

Whilst the trial will assess a “mainstream” clinical service, the aim is to target Maori and the most deprived in the community. To achieve this aim we will use identified facilitators that enable Indigenous people’s participation such as relationship and partnership building, involvement of Indigenous staff, the use of Indigenous knowledge models (such as He Korowai Oranga: the Maori Health strategy and the Whanau Ora [healthy families] tool) [22, 23], targeted recruitment techniques (such as working with Maori health workers within the community to engage with families) and adapting study material [24].

All children referred will be seen in the family (whanau) home by the Healthy Lifestyles Coordinator (a health professional trained in focussed weight-related assessment, supported by a Paediatrician). This design aspect allows the trial to run as a community-based service yet with a full clinical component to it. Removal of a hospital-based appointment with a specialist was designed to enable access to the service for larger numbers and minority groups, and to avoid “medicalisation” of the process. Given the service is targeting Maori and those from lower socio-economic areas, ensuring accessibility and appropriateness are crucial to the study design, without compromising clinical care.

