### Assessments

Assessments will be completed at six monthly intervals for 2 years from enrolment. Information will be gathered regarding ethnicity, past medical history, medical conditions and family history. Written informed consent will be obtained to take part in the trial and to share collected information between Sport Taranaki (the regional sports trust) and the Health Board. This will be from the participant if age-appropriate, or where the participants are children, a parent/guardian. Table 2 shows the key elements of the assessments undertaken.

**Table 2 Tab2:** Assessment information for all participants

Key assessments	Baseline	6 months	12 months	18 months	24 months
Resting heart rate	✓	✓	✓	✓	✓
Blood pressure^a^	✓	✓	✓	✓	✓
Height^b^	✓	✓	✓	✓	✓
Weight^c^	✓	✓	✓	✓	✓
Waist circumference^d^	✓	✓	✓	✓	✓
Hip circumference^e^	✓	✓	✓	✓	✓
Peak flow^f^	✓	✓	✓	✓	✓
Acanthosis nigricans screen	✓	✓	✓	✓	✓
Ear, nose and throat examination^g^	✓	✓	✓	✓	✓
Self report of Tanner pubertal stage^h^	✓	✓	✓	✓	✓
Accompanying adult’s height and weight	✓		✓		✓
Questionnaires^i^	✓	✓	✓	✓	✓
Blood sampling^j^	✓		✓		✓

Technical/procedural information: ^a^using Welch Allyn portable sphygmomanometer with flexiport reusable blood pressure cuffs of appropriate size, ^b^to 0.1 cm using average of three readings on Seca 213 portable stadiometer, ^c^to 0.1 kg using Seca 813 digital scales, ^d^Seca 201 standard measuring tape (at mid-point between the lower margins of the rib and the top of the iliac crest to 0.1 cm at end of normal expiration) [52]), ^e^widest girth, ^f^using Mini Wright peak flow meter, ^g^using Welch Allyn portable auroscope, ^h^or from parent in very young children [31], ^i^apart from RFC questionnaire (only performed at baseline), ^j^fasting insulin, fasting glucose, liver function tests, C-reactive protein, glycated Haemoglobin (HbA1c), and fasting lipids

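### No masking is stated for the assessor who takes the height and weight behind the primary outcome, although the listed programme staff are other people; partial masking would be cheap

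*Protocol article*

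**What the plan says.** Methods/Design gives the masking status: "Whanau Pakari is an unblinded randomised controlled clinical trial being conducted in Taranaki, New Zealand". The Abstract says the same, and no section describes masking of the person who measures outcomes.

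Data collection names that person: "The Healthy Lifestyles Coordinator will collect all data (apart from physical activity assessments) in the home assessments". Recruitment gives the setting: "All children referred will be seen in the family (whanau) home by the Healthy Lifestyles Coordinator". Table 2 schedules height, weight, waist, blood pressure, heart rate and questionnaires at baseline and at 6, 12, 18 and 24 months. Height is taken "to 0.1 cm using average of three readings on Seca 213 portable stadiometer", weight on digital scales and waist with a tape.

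Primary outcome: "The primary outcome measure is the change in BMI SDS in the intervention group compared with the control group". It is assessed at each of the four follow-up visits.

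On delivery of the programme, the Intervention section says: "It will be administered by a physical activity coordinator, community dietitian, and psychologist: all staff members within the Whanau Pakari team". The Healthy Lifestyles Coordinator is not on that list. Table 3 ticks the six-monthly assessments, with advice and feedback, for both arms. It also shows an optional keyworker in the intervention arm only and does not say who fills that role.

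The Study arms section has every child in both arms discussed by the multi-disciplinary team every six months. Data collection adds a database page on which the team reviews each participant's results.

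**The concern.** Families and session staff cannot be masked in a trial of this kind, but an assessor who delivers no sessions might be. The article separates the two roles in its staffing and does not use that separation to protect the measurements. It gives no reason why not.

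An assessor who expects the programme to work can influence a measurement without intending to, for example through posture at the stadiometer, tape position at the waist, a repeated blood pressure reading, or prompting in a food recall. If this differs between arms, it becomes part of the estimated effect. The mixed model under Data analyses adjusts for age, gender, socioeconomic status, ethnicity and readiness, and none of these can separate a measurement shift from a treatment effect.

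Taking change from baseline does not help either. The Randomisation section places assessment before allocation, so the baseline value is free of this bias while all four follow-up values are open to it. The bias would not cancel.

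Small shifts matter because the Sample size section cites literature in which a change of 0.1 BMI SDS is beneficial, and it hopes to show differences smaller than the 0.5 SDS used for planning.

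**Working it through.** **1. The plan's own figure.** The inputs under Sample size are a difference of 0.5 SDS, SD 1.3, 80 % power, and the 5 % level (taken as two-sided).

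n per group = 2 × (1.960 + 0.842)² × 1.3² / 0.5² = 106.1, so 107. Power at 107 is 80.3 %. With 10 % dropout, 107 / 0.9 = 118.9, so 119, against 120 stated. The figure reproduces. Masking does not affect it; it fixes the scale for step 4.

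**2. What the text establishes about the assessor.**

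| Question | Where | Answer |
|---|---|---|
| Who takes height, weight, waist and blood pressure? | Data collection; Table 2 | Healthy Lifestyles Coordinator, in the home |
| Is this role masked? | Abstract; Methods/Design | Trial unblinded; no assessor masking described |
| Does the Coordinator know allocation? | – | Not stated |
| Is the Coordinator listed as delivering the programme? | Intervention | No; keyworker role unassigned |
| How could allocation become known? | Study arms; Data collection | Team meetings, team database page, families at the visit |
| How many Coordinators? | Background; Data collection | Singular wording only ("It provides a trained roving community coordinator to meet families in their homes"); headcount not given |

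**3. How far a height shift moves BMI SDS.** The documents give no reference parameters and no figure for measurement error. The L, M and S values and the three example children below are therefore assumptions.

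z = ((BMI/M)^L − 1) / (L × S), with BMI = weight / height².

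| Child (assumed) | L, M, S (assumed) | BMI | z | Change for +0.2 cm | +0.5 cm | +1 cm |
|---|---|---|---|---|---|---|
| 125 cm, 36 kg | −1.8, 15.6, 0.09 | 23.04 | 3.113 | −0.018 | −0.044 | −0.089 |
| 140 cm, 53 kg | −1.9, 16.6, 0.12 | 27.04 | 2.650 | −0.009 | −0.024 | −0.048 |
| 160 cm, 80 kg | −1.6, 19.0, 0.13 | 31.25 | 2.639 | −0.009 | −0.022 | −0.044 |

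Relative to 0.1 SDS, that is about 9 to 18 % for 0.2 cm, 22 to 44 % for 0.5 cm, and 44 to 89 % for 1 cm. Relative to the planning difference of 0.5 SDS, 0.2 cm is at most about 4 % (0.018 / 0.5). Only a shift that differs systematically between arms counts; random reading error adds noise, not bias.

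**4. Effect on the type I error, as an illustration.** Assume no true effect, 107 per group, and a between-arm bias b. Then SE = SD × √(2/107), and the two-sided rejection rate is Φ(b/SE − 1.96) + Φ(−b/SE − 1.96).

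| SD of change | SE | b = 0.02 | b = 0.05 | b = 0.10 |
|---|---|---|---|---|
| 1.3 (protocol) | 0.178 | 5.1 % | 5.9 % | 8.7 % |
| 0.5 (assumed) | 0.068 | 6.0 % | 11.3 % | 31.0 % |

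With the protocol's SD the inflation is slight unless the bias is large. If changes vary less than planned, the same bias does more harm.

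**The case against.** The best defence is that this is an openly declared choice in a trial of a real-life service, and that calling it unblinded is candid. Much of that defence stands.

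- **Knowledge of allocation.** A reader might infer that a single Coordinator knows every child's arm. The text does not say so. It follows only from the word unblinded, the silence on masking and singular wording. What can be said is that nothing prevents it.
- **Feasibility.** A reader might infer that the Coordinator could be fully masked with no extra staff. That is not documented. Families who attend weekly sessions may reveal their arm, particularly when asked about diet and activity. The unassigned keyworker role also means that complete separation from the intervention is not established.
- **Breadth.** It would be too much to say that almost every outcome is exposed. Physical activity assessments are excepted from the Coordinator's collection. Glucose, HbA1c, insulin and lipids come from blood samples. Weight is read from digital scales. The mode of questionnaire administration is not given, and at least one is a self-report form.
- **Size.** A systematic 1 cm difference between arms is not supported by the documents. Averaging three readings reduces random error, although it does not remove a consistent lean.
- **Clinical role.** The Coordinator's home assessment replaces a hospital visit, so any change must leave clinical review intact.

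These points limit the strength of the concern and the claims that can be made for a remedy. They do not explain why measurements behind the primary outcome should have no protection where some is available. An article may leave measurement detail to a full protocol, but this one positively states an unblinded trial and names the assessor.

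**Conclusion.** The point holds as a design weakness of modest and unknown size. The trial is unblinded with no stated assessor masking. The person who takes the height and weight behind BMI SDS, and also waist, blood pressure and other non-laboratory home measurements, is not among the listed programme staff. The separation needed for at least partial masking is therefore largely in place and unused.

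The documents give no estimate of measurement bias. Under the assumed reference values, plausible effects run from about 0.01–0.02 BMI SDS for a 0.2 cm systematic height difference to 0.04–0.09 for 1 cm, the latter being an outer illustration. The lower end is small against the 0.1 SDS the protocol describes as beneficial; the upper end is not. Waist and any interviewed diet items are more exposed, weight less so.

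The documents do not show that bias will occur, or that masking would be complete. The case for change is that some protection costs little and that differential measurement error cannot be removed in analysis.

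**What to change.** Add to Data collection:

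1. At each follow-up visit, height, weight, waist and blood pressure are taken first, before questionnaires and feedback, and without sight of earlier values. This helps even where masking fails.
2. Allocation is not shown in the Coordinator's database view.
3. Arm-specific programme discussion at the team meeting is held without the Coordinator; full clinical review of every child continues as planned.
4. The keyworker role is not given to the Coordinator.
5. Families are asked not to mention their arm before the measurements are done.
6. At each visit the Coordinator records whether allocation has become known, and how.

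Keep describing the trial as open, with assessor masking attempted and its success reported. Calling it assessor-masked would overstate the protection. List unmasked assessment as a limitation where masking fails; at present the only limitation the Discussion labels as such is self-reported pubertal stage. If the sponsor judges any step infeasible, the article should say so and why.

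The cost is a change to database permissions, the meeting agenda and the visit order. The main drawback is that masking will be only partial, because some families will disclose.
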